# Web-based cognitive bias modification for problem drinkers: protocol of a randomised controlled trial with a 2x2x2 factorial design

**DOI:** 10.1186/1471-2458-13-674

**Published:** 2013-07-20

**Keywords:** Problem drinking, Alcohol, Cognitive bias modification, Implicit cognition, E-health intervention

## Abstract

**Background:**

The automatic tendency to attend to, positively evaluate and approach alcohol related stimuli has been found to play a causal role in problematic alcohol use and can be retrained by computerised Cognitive Bias Modification (CBM). In spite of CBMs potential as an internet intervention, little is known about the efficacy of web-based CBM. The study described in this protocol will test the effectiveness of web-based CBM in a double blind randomised controlled trial with a 2 (attention bias retraining: real versus placebo) x 2 (alcohol/no-go training: real versus placebo) x 2 (approach bias retraining: real versus placebo) factorial design.

**Methods/design:**

The effectiveness of 12 sessions of CBM will be examined among problem drinkers aged 18–65 who are randomly assigned to one of the eight CBM conditions, after completing two modules of a validated cognitive behavioural intervention, *DrinkingLess*. The primary outcome measure is the change in alcohol use. It is expected that, for each of the CBM interventions, participants in the real CBM conditions will show a greater decrease in alcohol use than participants in the placebo conditions. Secondary outcome measures include the percentage of participants drinking within the limits for sensible drinking. Possible mediating (change in automatic biases) and moderating (working memory, inhibition) factors will be examined, as will the comparative cost-effectiveness of the various CBM strategies.

**Discussion:**

This study will be the first to test the relative efficacy of various web-based CBM strategies in problem drinkers. If proven effective, CBM could be implemented as a low-cost, low-threshold adjuvant to CBT-based online interventions for problem drinkers.

**Trial registration:**

Netherlands Trial register: NTR3875.

## Background

Problematic alcohol use is highly prevalent and is associated with substantial costs for both the individual and society [1]. This calls for (cost-) effective interventions targeting the early stages of the disease process. Web-based interventions might meet these demands, by providing effective, low-cost interventions aimed at reducing problem drinking [2,3]. That said, the effectiveness of web-based interventions might be limited by their traditional focus on altering conscious (i.e. intentional, controlled) aspects of information processing, while many recent theories of addiction underscore the complementary role of more automatic, less intentional processes in the aetiology and maintenance of substance use problems [4-6]. According to dual process theories, repeated alcohol use can cause automatic (i.e. fast, less conscious) biases in information processing: alcohol cues selectively capture attention (attentional bias), activate positive associations in memory (memory bias), and elicit automatic approach tendencies (approach bias). These biases have been found to predict alcohol use [7,8], especially in people with low working memory [9,10], or poor response inhibition [11,12]. Importantly, these biases are largely unaffected by interventions aimed at altering conscious information processing [13,14], suggesting that interventions for problem drinkers will be more effective when both controlled and automatic processes are addressed.

During the past decade, a set of computerised training programs has been developed aimed at altering automatic cognitive biases, collectively called Cognitive Bias Modification (CBM). CBM has been found effective at altering attentional bias [15-18], memory bias [19,20], and approach bias [21-23], often with associated impacts on alcohol use. While CBM was first employed to test the causal role of automatic processes in alcohol use, researchers have now begun to examine CBM’s relevance for therapeutic intervention. Three studies have investigated the effects of CBM as an add on to face-to-face treatment, showing favourable effects on treatment duration [16] and relapse [21,23] among patients with alcohol dependence. While the promising effects of ‘offline’ CBM as a supplement to traditional interventions point to the possible value of ‘online’ CBM as an addition to current web-based interventions, little is known about the effectiveness of web-based CBM (but see [24] for an example of online working memory training among problem drinkers). This is surprising given the fact that CBM procedures were all developed as computerised tasks that require little explanation, thereby facilitating their suitability as web-based self-help interventions. Furthermore, in the field addiction, no studies have yet been published on the effects of combining different CBM interventions, though this is likely to maximize its efficacy.

### Aims and hypotheses

The aim of the current study is to investigate the effectiveness of three online CBM interventions: attentional bias retraining, alcohol/no-go training (targeting memory bias), and approach bias retraining. Problem drinkers receive 12 sessions of either the active or the placebo version of all three training programs, after completing the first two modules of an evidence-based online cognitive behavioural therapy (CBT) based intervention, *DrinkingLess*[25]*,* consisting of personalised feedback on one’s alcohol use and setting personal goals related to alcohol use, in order to increase motivation to change. The main goal of the study is to test the added effects of the CBM interventions on alcohol use at 3 months after the intervention, with changes in the number of alcoholic drinks consumed in the past two weeks as the primary outcome measure. It is expected that, for each of the CBM interventions, participants in the intervention conditions will show a greater decrease in weekly alcohol use than participants in the placebo conditions. Furthermore, each CBM intervention is hypothesised to decrease or reverse the specific bias it trains and these changes are expected to mediate the effects on alcohol use. Spill-over effects of each specific CBM intervention to other biases will be explored, as will the effects of the joint exposure to the various combinations of CBM interventions. In order to answer the question of “what works for *whom*?”, possible moderators will be examined. In line with dual process models, it is expected that participants with strong automatic biases and/or low working memory capacity and inhibitory control will benefit more from CBM than participants with weaker biases and/or stronger executive functions (as was found for CBM both in addiction [21] and in anxiety [26,27]). A better understanding of the relative contribution of each CBM version on treatment outcome is also expected to come from examining the cost-effectiveness of CBM interventions. Knowledge about the most effective CBM version(s) may have important implications for making choices in the implementation of CBM in health care.

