## Methods/design

### Trial design

The (cost) effectiveness of attentional bias retraining, alcohol/no-go training, and approach bias retraining will be studied in a 2×2×2 factorial design. This will allow us to explore possible additive or multiplicative effects of different combinations of CBM, as well as the related question to what extent retraining one bias will produce changes in other automatic biases; issues which not only have clinical relevance, but also important theoretical implications (see for example [28,29]). Participants will receive either the active or the placebo version of all three CBM interventions, amounting to eight conditions (see Figure 1). Prior to the training, participants will complete the first two modules of the *DrinkingLess* program [25]*.* Intervention effects will be tested directly after the intervention and 3, 6 and 12 months later. The expected timeline for trial completion and reporting the results is presented in Figure 2.

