### Participants and procedure

To ensure the ecological validity of the sample, participants will be recruited through sources that are comparable to how internet interventions are generally promoted in the Netherlands: the *DrinkingLess* website, websites related to alcohol abuse, newspaper articles, a television documentary on CBM for addiction, the website of the ADAPT lab, and word of mouth communication with existing participants. Interested participants are invited to create an account on the intervention website (http://www.test.uva.nl/toptrainingen), after which they read the information letter, a copy of which is automatically sent to them by e-mail. Participants who sign the online consent form then complete a brief screening for eligibility. Participants will be included if they: (a) have an Alcohol Use Disorders Identification Test (AUDIT [30]) score of 8 or above (b) have drunk more than 21 drinks (men) or 14 drinks (women) a week in the past two weeks, as assessed with the Timeline-Follow-Back (TLFB) method (c) are between 18–64 years old (d) have (almost) daily internet access and (e) do not receive professional treatment for problem drinking at the start of the study. Participants with an AUDIT score of >19 receive a message warning them that abrupt abstaining can have mental and physical consequences, and advising them to contact their General Practitioner in case of withdrawal symptoms. Eligible participants then complete the baseline assessment and two modules of *DrinkingLess*. The next day, they are invited to complete the first CBM training session. Participants have three days to complete each session, allowing them to complete the 12 training sessions in about 5 weeks. One day after the last training session, participants are invited to complete the post-intervention assessment. Follow-up assessments are conducted at three, six and twelve months after the intervention. The study has been approved by the Ethics Committee of the psychology department of the University of Amsterdam and registered at the Netherlands Trial register (NTR3875).

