### Primary and secondary outcome measures

The main outcome measure, the change in number of drinks consumed in the past 14 days three months after the intervention compared to baseline, will be assessed using the TLFB method [35]. Secondary outcome measures are: changes in automatic cognitive biases as assessed with the attentional bias, alcohol/no-go and approach bias tasks described above. Generalisation effects of attentional bias and approach bias training to other measures will be assessed with the alcohol Stroop task (described above) and the brief Implicit Association Task (bIAT, [47,48]), which is used to measure the strength of both approach associations and positive (valence) associations with alcohol. In the bIAT, participants are required to decide whether or not the exemplar word in the middle of the screen belongs to one or two focal categories at the top of the screen, by pushing the designated ‘yes’ or ‘no’ buttons (‘e’or ‘i’) on the keyboard. As in the study of Menatti et al. [47], the typical 7 block structure of the IAT was maintained, but with fewer trials per block. In the first block (12 trials) names of alcoholic (wine, beer, vodka) or non-alcoholic drinks (coke, water, juice) have to be classified as either belonging to the category ‘alcohol’ or not. In the second block (12 trials) exemplars have to be classified as either pleasant (funny, cheerful, sociable) or not (nauseous, sad, tired). In the third block (12 trials) and fourth (24 trials), the target (alcohol) and attribute (pleasant) categories are combined. In the fifth block (12 trials), the reversed attribute category, unpleasant, is practiced and then combined with the target category (alcohol) in the sixth (12 trials) and seventh block (24 trials). The approach bIAT follows the same structure, with the attributes ‘approach’ (grab, touch, take) ‘avoid’ (let go, avert, ignore). The order of the two versions of the bIAT, as well as the order of the combined blocks within the bIAT, and the contingency between the response (yes/no) and the buttons (i/e) is counterbalanced across participants. The outcome measure is the standardised difference in latencies (*D* score*)* between the different combined blocks.

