### Sample size

G*Power 3.1.5 [54] was used to calculate the sample size for a power of 0.8 for each main effect or interaction (all Numerator *df* = 1), at an alpha of 0.05. Based on a meta-analysis of internet self-help interventions for problem drinkers a medium effect size (*f* = 0.25) would be expected [2], but the effect size may be reduced by the active control conditions and the two modules of the *DrinkingLess* intervention that all participants receive. A small-to-medium effect size of *f* = 0.15 was therefore specified, for which the required sample size is 351 (see Figure 7).

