### Clinical evaluation

All analyses will be conducted in agreement with the intention to treat principle, as per the CONSORT statement [56]. To that end, missing endpoints will be imputed using the EM algorithm [57]. The main effects and interaction effects of the CBM interventions on the primary and the continuous secondary outcome measures will be analysed with a 2 (attentional bias retraining: active/placebo) × 2 (alcohol/no-go training: active/placebo) × 2 (approach bias retraining: active/placebo) × 2 (time: pre-intervention/3 month follow-up) repeated measures ANOVA.

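### The planned two-time-point ANOVA tests raw change in an open-ended drink count without adjusting for baseline drinking or the minimisation factors, which is valid but likely to waste power

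*Protocol article*

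**What the plan says.** The outcome is given twice in the protocol article. Aims and hypotheses describes the study "with changes in the number of alcoholic drinks consumed in the past two weeks as the primary outcome measure", and Primary and secondary outcome measures specifies "the change in number of drinks consumed in the past 14 days three months after the intervention compared to baseline", measured by TLFB.

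Under Participants and procedure, people enter only if they "have drunk more than 21 drinks (men) or 14 drinks (women) a week in the past two weeks", that is, above 42 (men) or 28 (women) drinks per 14 days. No upper limit on drinking is given. High severity does not exclude: "Participants with an AUDIT score of >19 receive a message warning them".

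Clinical evaluation names one analysis for the primary and continuous secondary outcomes: the three training factors crossed with "2 (time: pre-intervention/3 month follow-up) repeated measures ANOVA". No covariate is listed. Randomisation states that allocation is minimised on gender and AUDIT level (8–19 versus above 19).

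Sample size aims "for a power of 0.8 for each main effect or interaction", with f = 0.15, alpha 0.05 and 351 participants. It gives no SD or difference in drinks. Trial design says the factorial layout serves to "explore possible additive or multiplicative effects of different combinations of CBM".

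**The concern.** With two time points, each training-by-time F test is the same as a test of that training on the change score. A change score fixes the coefficient of baseline at one. If participants who start higher also fall further, the true coefficient is below one, and the mismatch stays in the error term.

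This outcome invites that mismatch. Eligibility is judged on a TLFB count, so some regression to the mean is expected in every arm. All arms receive two *DrinkingLess* modules, so drinking may fall in all of them. With no ceiling, a few people with very high counts may contribute changes far larger than the rest.

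All three primary hypotheses rest on this test, so what is at stake is the chance of detecting a real training effect. A smaller issue is that interactions on the raw scale are judged only against additivity in drinks, although Trial design also mentions multiplicative effects.

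**Working it through.** **1. The plan's own figure.** With f = 0.15, λ = N·f² = 351 × 0.0225 = 7.90. The noncentral F with 1 and 343 df at alpha 0.05 gives power 0.800. The stated 351 is reproduced.

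**2. Change score against baseline adjustment.** Let σ₀² be the baseline variance, β the slope of the follow-up count on the baseline count, and τ² the residual variance.
- Error variance of the change score: τ² + σ₀²(1 − β)²
- Error variance after adjustment: τ²

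The excess, σ₀²(1 − β)², is never negative and vanishes only at β = 1. A long upper tail makes σ₀² large and so enlarges it.

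As an illustration, assume equal variances at both times and correlation ρ. The ratio of adjusted to change-score variance is then (1 + ρ)/2. Suppose f = 0.15 is exactly right for the change score, so that planned power is 0.80. Adjusted power then uses λ = 7.90 ÷ [(1 + ρ)/2]:

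| ρ (assumed) | variance ratio | λ | adjusted power |
|---|---|---|---|
| 0.5 | 0.75 | 10.53 | 0.90 |
| 0.7 | 0.85 | 9.29 | 0.86 |
| 0.9 | 0.95 | 8.31 | 0.82 |

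At ρ = 0.5, adjustment reaches the planned power with about 351 × 0.75 = 263 participants.

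**3. Simulation at N = 351, one training factor.** The article gives no distribution, so every input here is an assumption: log-normal baselines cut at 42 and 28 drinks, and various scatter, abstinence and effect forms. Power for raw change, then raw scale with baseline covariate:
- 20% reduction, 3% abstinent at follow-up: 0.48 and 0.59; with less scatter, 0.69 and 0.85 (11 and 16 points)
- 25% reduction, more scatter: 0.48 and 0.55 (7 points)
- 20% reduction, other baseline medians, 10% and 20% abstinent: 0.55 and 0.64; 0.42 and 0.50 (9 and 8 points)
- Benefit concentrated in heavy drinkers: 0.45 and 0.54 (9 points)

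The gain follows the slope, as step 2 predicts. Take baseline log-SD 0.8 with follow-up equal to 0.75 × baseline × log-normal noise of log-SD s, so that β = 0.75·exp(s²/2):
- s = 0.3: β = 0.78; power 0.46 and 0.61
- s = 0.5: β = 0.85; power 0.53 and 0.58
- s = 0.7: β = 0.96; power 0.54 and 0.56

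Other settings with a slope near one showed gains of 0 to 3 points. In none was adjustment worse by more than simulation error.

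**4. Weight of the heaviest drinkers.** With assumed log-SD 0.4 to 0.8, the top tenth at baseline carry about 28–59% of the sum of squares of raw change, a majority only at the widest spread. Type I error of the raw-change test stayed near 0.05.

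**5. Log link against raw scale.** Raw change, adjusted raw scale, negative-binomial log link with robust SE:
- Proportional effect: 0.68, 0.75, 0.80
- Benefit concentrated in heavy drinkers: 0.45, 0.54, 0.37

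**6. Interaction scale.** Two trainings that each cut drinking by 20% independently give 60, 48, 48 and 60 × 0.8 × 0.8 = 38.4 drinks. The additive contrast is 38.4 − 48 − 48 + 60 = +2.4 drinks. On the ratio scale it is 38.4 × 60 ÷ (48 × 48) = 1, which is no interaction.

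**The case against.** The strongest reply is that power was set on a standardised effect. If f = 0.15 holds for the analysed quantity, power is about 0.80 however skewed the counts are (0.77–0.82 in simulation). That is correct, so no shortfall against the plan's own assumption is shown. It does not defend the change score, because the same true effect would be detected more often after adjustment.

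A second reply is that absolute change is a legitimate target: Aims and hypotheses predicts a greater decrease in weekly use. This stands, and the fix keeps the absolute scale.

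A third is that an analysis plan, not shown, may add covariates, transformations or count models. The lack of distribution checks is indeed no fault of an article. But the article does name the primary test, and what it names is an unadjusted change comparison.

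A reader might infer more: that the heaviest drinkers dominate the analysis, that power is certainly lost to the raw scale, and that a log-link model must replace it. The documents do not support this. They give no SD, skew, abstinence rate or effect form, and step 5 shows the ranking of the two scales reversing with the form of the effect. Aims and hypotheses itself expects larger benefit in some participants than in others. Nor does the entry floor bias the comparison: it applies before randomisation, to all arms alike. Finally, Trial design speaks only of exploring multiplicative effects, so the interaction point is minor.

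**Conclusion.** The concern holds as a point of efficiency. The planned test is valid and unbiased between arms, but it fixes the baseline coefficient at one and ignores both minimisation factors. The size of the loss depends on the slope of follow-up on baseline, which the article does not give. It was about 7 to 16 points of power at 351 participants in most assumed settings where the slope was clearly below one, and close to nothing where it was near one. The direction does not depend on those assumptions, since the excess variance cannot be negative. Disproportionate influence of heavy drinkers is likely if the counts are right-skewed, but it is not established. Whether a log-link model would do better remains open.

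**What to change.** In Clinical evaluation, make the primary analysis a linear model of the 3-month TLFB 14-day count with the three training factors and their interactions, and with baseline 14-day count, gender and AUDIT level as covariates. Use robust standard errors and report the adjusted difference in drinks per 14 days for each training.

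Add one prespecified sensitivity analysis: a log-link count model, such as negative binomial, with log baseline count, the same other covariates and robust standard errors. State that multiplicative combinations are read from this model and additive ones from the primary model.

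The cost is wording only. All covariates are already collected, and outcome, sample size and absolute scale are unchanged. The change should be made before any unblinded outcome data are examined.

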## Methods/design

### Trial design

The (cost) effectiveness of attentional bias retraining, alcohol/no-go training, and approach bias retraining will be studied in a 2×2×2 factorial design. This will allow us to explore possible additive or multiplicative effects of different combinations of CBM, as well as the related question to what extent retraining one bias will produce changes in other automatic biases; issues which not only have clinical relevance, but also important theoretical implications (see for example [28,29]). Participants will receive either the active or the placebo version of all three CBM interventions, amounting to eight conditions (see Figure 1). Prior to the training, participants will complete the first two modules of the *DrinkingLess* program [25]*.* Intervention effects will be tested directly after the intervention and 3, 6 and 12 months later. The expected timeline for trial completion and reporting the results is presented in Figure 2.

**Figure 1 F1:**
[figure not shown]
Participant flowchart.

**Figure 2 F2:**
[figure not shown]
Expected timeline for completion and reporting.

### Participants and procedure

To ensure the ecological validity of the sample, participants will be recruited through sources that are comparable to how internet interventions are generally promoted in the Netherlands: the *DrinkingLess* website, websites related to alcohol abuse, newspaper articles, a television documentary on CBM for addiction, the website of the ADAPT lab, and word of mouth communication with existing participants. Interested participants are invited to create an account on the intervention website (http://www.test.uva.nl/toptrainingen), after which they read the information letter, a copy of which is automatically sent to them by e-mail. Participants who sign the online consent form then complete a brief screening for eligibility. Participants will be included if they: (a) have an Alcohol Use Disorders Identification Test (AUDIT [30]) score of 8 or above (b) have drunk more than 21 drinks (men) or 14 drinks (women) a week in the past two weeks, as assessed with the Timeline-Follow-Back (TLFB) method (c) are between 18–64 years old (d) have (almost) daily internet access and (e) do not receive professional treatment for problem drinking at the start of the study. Participants with an AUDIT score of >19 receive a message warning them that abrupt abstaining can have mental and physical consequences, and advising them to contact their General Practitioner in case of withdrawal symptoms. Eligible participants then complete the baseline assessment and two modules of *DrinkingLess*. The next day, they are invited to complete the first CBM training session. Participants have three days to complete each session, allowing them to complete the 12 training sessions in about 5 weeks. One day after the last training session, participants are invited to complete the post-intervention assessment. Follow-up assessments are conducted at three, six and twelve months after the intervention. The study has been approved by the Ethics Committee of the psychology department of the University of Amsterdam and registered at the Netherlands Trial register (NTR3875).

